### Trial design {8}

Our study will follow a randomised controlled trial (RCT) design with a single-blind approach. We will use parallel group superiority trial and unpaired group methods and conclude the investigation by assessing parameter changes within 12 weeks. A block randomisation method is utilised to allocate participants, generating blocks of two with a 1:1 ratio. Randomisation does not distinguish the occurrence of keloids based on skin colour as the research setting tends to have a homogenous population with skin tones typical of Southeast Asians, ranging from light to dark brown [49].

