### Eligibility criteria {10}

To qualify for our study, participants must be 18 years old or above and have keloid scars that measure 25 cm^2^ or less. Each participant must have at least one keloid that has lasted for at least 6 months, and they cannot take keloid medication for the past 2 months. Those who are unable to understand the patient and observer scar assessment scale (POSAS), refuse to participate, have nodular keloids, take antihypertensive medication, are pregnant, have a history of allergies, have active skin lesions in the keloid area, or have bleeding or scars are not eligible for the study. Additionally, we will exclude individuals who have undergone keloid treatment within the last month.

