### Outcomes {12}

The research inquiry will encompass an assessment of both primary and secondary outcomes. The primary outcome directed towards the evaluation of POSAS 3.0 scores. Throughout the study’s duration, we will systematically assess POSAS 3.0 scores at four specific time intervals: the initial baseline assessment upon participants’ first arrival, followed by subsequent evaluations at weeks 4, 8, and 12. This measurement directly correlates with the patient’s quality of life [52]. We will utilise the most up-to-date version of the POSAS 3.0 questionnaire, accessed at https://www.posas.nl. We have received approval from the POSAS team to use this questionnaire and have been granted a license via email. This questionnaire will be translated into Indonesian and tested for validity and reliability before being used in the study. Patients will complete the POSAS 3.0 questionnaire, which includes 16 items. Five of these items are about the current state of their scar tissue, and 11 questions are about how their feeling related to the scar tissue over the past week. Meanwhile, an observer will complete a different section of the questionnaire with seven items scored on a scale of 1 to 5. We will add the PSAS and OSAS scores to determine the total score. The minimum patient score is 16, while the highest score is 80. The minimum and maximum scores for observers are 7 and 35, respectively.

In the context of this study, secondary outcomes encompass the evaluation of erythema and pigmentation levels, as well as assessments of keloid area, thickness, and pliability. These secondary outcome measures at four different time points will be assessed concurrently with the primary outcome.

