The colour images will be captured using dermoscopy equipment from Heine® iC1 Germany, followed by image analysis. Dermoscopy is employed to capture colour images from three discrete regions, specifically focusing on the edges and central region. This process is iterated for precision, and subsequently, ImageJ image analysis computes the average colour quantification of the captured images. The same proficiently trained assistant will capture colour images using dermoscopy consistently during the entire duration of the study. Our team will utilise digital photography (Sony®α6000 Japan) and ImageJ image analysis software to examine the surface area. A trained assistant will take pictures of the keloid with appropriate camera lighting, and a ruler will be included in the shot to confirm the scale in ImageJ. The surface area changes will be measured in centimetres squared and evaluated at four different time points throughout the study.

A dedicated computer IT assistant, consistent throughout the study, will measure colour degrees and surface areas using ImageJ to maintain consistency.

High-frequency ultrasound (Hitachi® Arietta s60 Japan) will be employed to assess keloid thickness. The linear probe will be operating at frequency of 5–12 MHz [50]. Throughout the study, the same radiologist will consistently measure the thickness of the keloid in centimetres, specifically assessing it at the same three points as during the initial measurement. Subsequently, the obtained measurements will be averaged for analysis. The pliability of keloids is measured using a manual tonometer called durometer type oo (Tecklock® Japan). A trained assistant will use the tonometer on three different areas of the keloid and calculate the average in durometer units displayed on the device. During the study, we will also monitor for any potential side effects arising from the interventions.

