### Sample size {14}

The sample size determination depends on the specific criteria for comparative research. The variable type of the primary outcome data plays a significant role in deciding the appropriate sample size [50, 51, 53, 54]. The primary outcome is the changes in POSAS 3.0 scores, considered continuous data. Effect size measurement will be the mean difference. The research involved unpaired or two groups receiving different treatments, with the outcome being measured multiple times. As a result, a specific formula was utilised below [55].

This study maintains a 5% type I error dan is powered to have an 80% chance of detecting a minimum of 4 different scores of POSAS. Thus, a sample size of 18 was calculated for the two-sided approach. Adjusted sample size to anticipate a 20% dropout is obtained from the formula N1 = *n*/(1-d), with *n* as the sample size required per formula and d as the dropout rate [56]. Thus, the final sample will be 23 for each group treatment.$${n}_1={n}_2=Y\left[2{\left(\frac{\left[{z}_{\alpha }+{z}_{\beta}\right]s}{x_1-{x}_2}\right)}^2\right]$$

*Z*
_*α*_ = 5% (1.96), *Z*_*β*_ = 20% (0.84), *S* (standard deviation) = 4.8, *x*1-*x*2 (the minimum difference in POSAS scores between the two treatment groups) = 4, *Y* (correction factor for multiple assessments) = 0.8.

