A trained personnel will acquire a surface area photograph using a digital single-lens reflex (DSLR) camera and subsequently transmit it anonymously to the computer IT assistant. The IT assistant will then utilise the ImageJ image analysis tool to ascertain the measurement, yielding an average value in millimetre squares, which will be meticulously documented in a CRF. This information will be subsequently transmitted to an online form accessible solely by the data analyst, who will be granted access exclusively to the participant code while remaining uninformed about the intervention particulars. The change surface area with photographic planimetry is reliable for assessing an area of approximately or equal to 25 cm^2^ [63]. Pictures were taken using a versatile single-lens reflex camera that can capture better-quality images than other types of cameras [64]. In measuring the area of the wound, this device provides fast, accurate results and good reliability [65].

Keloid thickness in millimetres is assessed through high-frequency ultrasound (HFU) conducted by an intervention-blinded radiologist, utilising solely the participant’s code number in a designated CRF. Following this, the obtained data will be compiled by a nurse assistant, and the data entry process into an online form will be conducted by a non-research team member, who will subsequently transmit it to the data analyst for further analysis. The high-frequency ultrasound method is a non-invasive, affordable, and valuable method for evaluating the clinical efficacy of scar tissue treatment [66–69].

A trained assistant will measure the pliability of the keloid using a durometer type oo from three different areas. The result will be recorded in a CRF, and a non-research member will input the data into an online form to the data analyst without any known intervention. The tool will undergo routine calibration. Tissue tonometry is a simple, repeatable, and objective method of measuring tissue density and is clinically useful for assessing individual scar tissue [70–72].

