## Statistical methods

### Statistical methods for primary and secondary outcomes {20a}

Statistical analysis will be done by Statistical Package for Social Science (SPSS) version 24. An analysis of the demographic data of the research subjects is planned to be conducted using descriptive statistics. The findings presentation will utilise frequency and percentage tables. Mean values are presented with standard deviation for continuous variables with a normal distribution. The normality of the data can be determined using the Shapiro-Wilk test. If the distribution is not normal, the median and interquartile range (IQR) are used. We conduct an analysis that compares the efficacy of a numerical variable in two groups and within a group, measured multiple times, using a generalised linear model analysis with alternative repeated Mann-Whitney analysis. Our study focuses on continuous variables for both primary and secondary outcomes. Our test had a power value of 80%, a confidence interval of 95% (95% CI), and a significance level of *p* < 0.05.

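### Keloid area, a secondary outcome, is stated as absolute cm² change with no baseline adjustment, which can cost power if lesion sizes vary widely and shrinkage is roughly proportional to size

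*Protocol article*

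**What the plan says.** All references are to the protocol article.

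- **Scale.** Outcomes {12}: "The surface area changes will be measured in centimetres squared and evaluated at four different time points throughout the study". The plans for assessment {18a} describe the same ImageJ reading as "yielding an average value in millimetre squares, which will be meticulously documented in a CRF". Both units are absolute, and they differ. No section expresses area relative to baseline.
- **Range of sizes.** Under Eligibility criteria {10}, participants must "have keloid scars that measure 25 cm^2^ or less". There is no lower limit.
- **Allocation.** Trial design {8} describes "generating blocks of two with a 1:1 ratio". Stratification by lesion size is not mentioned.
- **Analysis.** Statistical methods {20a} compares the arms "using a generalised linear model analysis with alternative repeated Mann-Whitney analysis". It names no covariate.
- **Role.** Outcomes {12}: "secondary outcomes encompass the evaluation of erythema and pigmentation levels, as well as assessments of keloid area, thickness, and pliability". Area is also listed among the parameters of the main goal in Objectives {7}. The sample size in {14} rests on POSAS alone.

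**The concern.** With no lower size limit, one trial can hold lesions of very different size. A 20% reduction is 0.20 × 1 = 0.2 cm² in a 1 cm² lesion and 0.20 × 25 = 5 cm² in a 25 cm² lesion. The same relative response therefore differs 25-fold on the stated scale. If response is roughly proportional, this spread enters the within-arm variance of cm² change and can hide a difference between the arms.

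A Mann-Whitney test on the changes does not remove the problem. Ranks of absolute change also follow starting size, and the standard test takes no covariate.

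Area deserves care because it is read from anonymised photographs by an assistant blinded to treatment. Participants, by contrast, know their treatment and supply 16 of the 23 items in the POSAS total.

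**Working it through.** **The plan's own figure.** The formula in {14} gives n = 0.8 × 2 × ((1.96 + 0.84) × 4.8 / 4)² = 1.6 × 3.36² = 18.06. The text says: "Thus, a sample size of 18 was calculated for the two-sided approach". With 20% dropout, 18 / (1 − 0.2) = 22.5, so 23 per arm. The stated numbers reproduce. They concern POSAS, and the article gives no figure for area. Taken from it below are 18 or 23 per arm and a two-sided test at 0.05 ("This study maintains a 5% type I error").

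**Assumptions needed for area.** The article gives neither a distribution of lesion size nor an expected shrinkage, so both must be assumed and varied.

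*Proportional response, log-uniform sizes up to 25 cm², 18 per arm.* Follow-up area = baseline × (1 − reduction) × log-normal noise, with reductions of 38% v 20% and a log SD of 0.25.

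| Analysis | Smallest lesion 1 cm² | Smallest lesion 5 cm² |
|---|---|---|
| t test on unadjusted cm² change | 35% | 61% |
| Mann-Whitney on cm² change | 44% | 61% |
| Raw area, baseline area as covariate | 60% | 75% |
| Log area, log baseline as covariate | 83-84% | 83-84% |

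With no true difference, every method rejects in about 5% of trials.

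*Proportional response, other size distributions, 18 per arm.* Mean reductions are 40% v 20%, 50% v 30% or 60% v 40% (SD 20 points), or 30% v 20% (SD 10 points). A t test on percentage change has about 83% power throughout. The last column is the share of within-arm variance of cm² change explained by baseline size.

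| Baseline sizes | Unadjusted cm² change | With baseline covariate | Share from baseline |
|---|---|---|---|
| Uniform 1-25 cm² | 37-54% | 71-72% | 34-58% |
| Skewed, median 4, cut at 25 cm² | 21-37% | 61-62% | 48-72% |
| Uniform 10-25 cm² | 68-76% | 79-80% | 14-28% |

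With 23 per arm, unadjusted power in the three rows is 46-65%, 27-46% and 78-86%.

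*Reverse case: cm² loss does not depend on size.* With a loss of 1.0 v 0.5 cm² (SD 0.5) and 18 per arm, unadjusted change has 82-83% power. Raw area adjusted for baseline has about 81%. Log area with log baseline has about 53% with a smallest lesion of 2 cm² and 72% with 5 cm². It falls further with smaller lesions, where the result also depends on how a vanished lesion is coded. Under constant loss generally, baseline explains only about 2-5% of the variance of cm² change.

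**Reading across.** The baseline covariate recovers much of the lost power under proportional response and costs 1 to 2 points under constant loss. The log scale gains most in the first case and loses substantially in the second.

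**The case against.** The strongest reply is that a unit of measurement is not an analysis. The quoted sentence in {12} sits among details of camera, ruler and software. A generalised linear model for repeated measurements can hold a baseline covariate or a log link, and {20a} does not say that the Mann-Whitney test is applied to absolute changes. A full analysis plan, which is not shown, may settle all of this. That stands as a limit: the article does not rule adjustment out. It does, however, state change in absolute area, and it names a fallback test that cannot take a covariate, so improving on the stated method is a fair point.

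Second, the power loss depends on the assumptions. This also stands. With lesions of 10 to 25 cm² the loss is modest, and under constant cm² loss there is none. Eighteen per arm assumes the full 20% dropout; 23 per arm raises every figure.

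Third, area is secondary and the trial is not sized for it. This stands too and limits the consequence.

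A reader might go further and infer that cm² change mainly measures starting size, or that a few large lesions decide the comparison. The article does not support either. Baseline's share of the variance runs from about 2% to 72% according to the assumptions. Nor is it telling that the 9 largest deviations of 36 carry 74-84% of the variance in such simulations, since purely normal data already give 71%.

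**Conclusion.** The point holds as a matter of precision on one secondary outcome. Under proportional shrinkage and widely varying sizes, with 18 per arm and a smallest lesion of 1 to 5 cm², power is about 35-61% for unadjusted cm² change against 60-75% with baseline area as covariate. Both conditions are assumptions. If sizes are similar the gain is small, and if cm² loss does not depend on size there is none.

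It would be tempting to call the area comparison biased, or to require the log scale as the only analysis. Neither follows. Randomisation keeps type I error near 5%, and a chance imbalance in size is reflected in the confidence interval. The log scale is a trade-off that rests on a response pattern the article does not give. The POSAS result and its sample size are unaffected.

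Separately, the area units in {12} and {18a} contradict each other. As 1 cm² is 100 mm², values recorded in mixed units would differ by a factor of 100.

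**What to change.** - In {12} and {20a}, analyse follow-up area with baseline area as a covariate, in place of unadjusted cm² change or a Mann-Whitney test on it. Report the adjusted between-arm difference with its 95% CI.
- Add the between-arm ratio of areas (percentage reduction), from log follow-up area with log baseline area as covariate, as a prespecified supportive analysis. State in advance how a lesion of zero area is handled, for example by a small offset.
- Use one area unit in {12}, {18a} and the case report form.

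The cost is wording only. Baseline area is already measured at the first visit, so no new data, visits or patients are needed. The covariate loses 1 to 2 points of power if cm² loss does not depend on size.

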### Participant timeline {13}

The schedule of enrolment, intervention, assessment, and visits for participants is presented in Fig. 1, following the SPIRIT figure.

**Fig. 1 Fig1:**
[figure not shown]
Schedule of enrolment, interventions, and assessments

### Sample size {14}

The sample size determination depends on the specific criteria for comparative research. The variable type of the primary outcome data plays a significant role in deciding the appropriate sample size [50, 51, 53, 54]. The primary outcome is the changes in POSAS 3.0 scores, considered continuous data. Effect size measurement will be the mean difference. The research involved unpaired or two groups receiving different treatments, with the outcome being measured multiple times. As a result, a specific formula was utilised below [55].

This study maintains a 5% type I error dan is powered to have an 80% chance of detecting a minimum of 4 different scores of POSAS. Thus, a sample size of 18 was calculated for the two-sided approach. Adjusted sample size to anticipate a 20% dropout is obtained from the formula N1 = *n*/(1-d), with *n* as the sample size required per formula and d as the dropout rate [56]. Thus, the final sample will be 23 for each group treatment.$${n}_1={n}_2=Y\left[2{\left(\frac{\left[{z}_{\alpha }+{z}_{\beta}\right]s}{x_1-{x}_2}\right)}^2\right]$$

*Z*
_*α*_ = 5% (1.96), *Z*_*β*_ = 20% (0.84), *S* (standard deviation) = 4.8, *x*1-*x*2 (the minimum difference in POSAS scores between the two treatment groups) = 4, *Y* (correction factor for multiple assessments) = 0.8.

### Recruitment {15}

To determine the number of participants required based on the sample size, the investigator will document all new and existing patients who meet the inclusion criteria in the outpatient dermatology clinic in the general hospital Syafira and extend an invitation to participate. If the number of patients still needs to be improved, the researcher will seek assistance from other dermatologists to refer potential keloid patients willing to participate in the study. Additionally, the researcher will publicly announce a call for participation from individuals with visible scars that meet keloid criteria through advertisement.

## Assignment of interventions: allocation

### Sequence generation {16a}

To carry out the study, a non-research team member will use computer-generated blocks of two for randomisation, ensuring a fair allocation of participants with a 1:1 distribution across both groups. One group will have 23 participants receiving a 5% LEG, while the other will receive 10 mg/ml TAC and 23 participants.

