## Methods: participants, interventions, and outcomes

### Study setting {9}

The study focused on patients aged 18 years and above, diagnosed with keloids, who visit the outpatient clinic of the dermatology department at The General Hospital of Syafira Pekanbaru, Riau, Indonesia, between August 2023 and April 2024.

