### Concealment mechanism {16b}

The allocation of treatment is hidden from both participants and investigators. Upon enrolment, participants are notified by the investigator that they will be allocated to one of two treatment groups according to an allocation list generated by a computerised system. Each participant will have the same probability of receiving either treatment. This sequence list is adjusted to the participant’s arrival time for the baseline examination at the hospital. The nurse assistant will keep the record list and determine the treatment received based on the numbered sequence list.

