## Assignment of interventions: blinding

### Who will be blinded {17a}

The outcome assessors and data analyst will be blinded to the treatment assignment. The assessors will evaluate the clinical changes such as the POSAS scores and degree of erythema and pigmentation, as well as the area, thickness, and pliability of the keloid. As the intervention’s nature makes it impossible to blind participants and staff to the allocation, they are instructed not to disclose the participant’s allocation status during follow-up assessments. A computer IT assistant and other outcome assessors who assess the POSAS score and the degree of erythema and pigmentation, area, thickness, and pliability of keloid will anonymously be blinded to the intervention. They will record the results in anonymously case report forms (CRFs) and input data into separate datasheets online. This will enable the researcher to analyse data without accessing information about the allocation.

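### Fixed blocks of two, with treatment visible to staff, make up to 23 of the 46 allocations predictable, so the stated concealment from investigators is not secured

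*Protocol article*

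**What the plan says.** The block size is fixed in two places. Under Trial design {8} the method is described as "generating blocks of two with a 1:1 ratio", and under Sequence generation {16a} "a non-research team member will use computer-generated blocks of two for randomisation". No other block size appears and no stratification factor is named. The planned totals are 46 participants: "One group will have 23 participants receiving a 5% LEG, while the other will receive 10 mg/ml TAC and 23 participants".

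There is one site. Study setting {9} describes patients who "visit the outpatient clinic of the dermatology department at The General Hospital of Syafira Pekanbaru".

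Concealment mechanism {16b} states: "The allocation of treatment is hidden from both participants and investigators". The mechanism it gives is a numbered list followed in the order in which participants arrive for the baseline examination: "The nurse assistant will keep the record list and determine the treatment received based on the numbered sequence list". Implementation {16c} places this nurse assistant at the outpatient clinic as an administrator, with access to patient identity and code number. Under Recruitment {15} it is the investigator who documents and invites eligible patients.

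Who will be blinded {17a} says that the intervention's "nature makes it impossible to blind participants and staff to the allocation". Outcome assessors and the data analyst are to be blinded.

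**The concern.** With 1:1 blocks of two, only two blocks are possible: gel then injection, or injection then gel. Once the first member of a pair has been treated, the arm of the second is settled. Secrecy of the list does not help, because the first treatment is visible to staff and the block size is in the protocol.

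Allocation concealment exists so that the decision to enrol a patient, and when, cannot depend on the arm the patient will receive. Here a recruiter who knew the preceding arm could, knowingly or not, bring forward or hold back a patient because of the arm that comes next. Patients also arrive by referral and advertisement, so the order of arrival is not wholly outside the team's control. Selection of this kind happens before any outcome is measured, so blinding the assessors and the analyst does not prevent it. In a trial of 46, a modest prognostic imbalance could move the estimated treatment effect noticeably.

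Keeping the numbered list inside the recruiting clinic adds a second, separate route to the same problem, although the article does not say that its holder recruits.

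**Working it through.** **Inputs.** Block size 2 and ratio 1:1 (Trial design {8}, Sequence generation {16a}). 23 per group (Sequence generation {16a}). SD 4.8, target difference 4 points, correction factor 0.8, two-sided 5% type I error, 80% power, 20% dropout (Sample size {14}). One clinic (Study setting {9}). Staff and participants open, assessors and analyst blinded (Who will be blinded {17a}).

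**The plan's own total.** n = 0.8 × 2 × ((1.96 + 0.84) × 4.8 / 4)² = 18.06, stated as 18. After dropout, 18 / (1 − 0.2) = 22.5, taken as 23 per group. The total of 46 makes 46 / 2 = 23 blocks of two. The stated total reproduces and is not affected by this point.

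**Predictability with blocks of two**, for someone who knows past allocations but has no list:
- First of a pair: probability 1/2 for either arm. Second of a pair: certain.
- Certain allocations: 23 × 1 = 23 of 46 (50%).
- Expected correct guesses: 23 × (1/2 + 1) = 34.5 of 46 (75%), against 23 of 46 (50%) by chance.
- Whoever holds the list knows all 46.

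**Comparison with other schemes.** For blocks of 4, even if the size is known, the chances of a correct guess at positions 1 to 4 are 1/2, 2/3, 2/3 and 1. They sum to 2.83, and 2.83 / 4 = 71%. The third position is certain with probability 1/3 and the fourth always, so 1.33 of 4 are certain. The same enumeration gives the row for 6. The mix was simulated with 20,000 runs, guessing whichever arm is behind overall.

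| Scheme | Certain, of 46 | Best guess correct |
|---|---|---|
| Fixed 2 | 23 (50%) | 75% |
| Fixed 4, size known | about 15.3 (33%) | 71% |
| Fixed 6, size known | 11.5 (25%) | 68% |
| Undisclosed mix of 4 and 6 | few | about 69% |

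**What steering could do (assumed scenarios).** The documents give no figure for the size or frequency of steering, so both are assumptions here. Suppose a share s of the 23 foreseeable participants is selected so that the score moves by η points in the direction that favours one arm: up by η if the participant goes to that arm, down by η if to the other. On average half of each arm is foreseeable, so one arm mean moves by +sη/2 and the other by −sη/2. The bias is therefore sη. The standard error of the difference is 4.8 × √(2/23) = 1.42. Simulation with no true effect (40,000 runs, 23 per arm, unadjusted t-test) gives:

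| Shift η | Share steered s | Bias (points) | Type I error |
|---|---|---|---|
| 1 | one third | about 0.3 | about 6% |
| 1 | half | about 0.5 | about 6% |
| 1 | all | about 1.0 | about 10% |
| 2 | one third | about 0.7 | about 7% |
| 2 | half | about 1.0 | about 10% |
| 2 | all | about 2.0 | about 27% |

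A bias of 1.0 is a quarter of the 4-point target difference (1.0 / 4 = 25%).

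**The case against.** The strongest defence is that duties are separated. Someone outside the research team generates the list, a nurse assistant keeps it, and the investigator who invites patients is said not to see it. That is a recognised arrangement. The article does not say who injects or dispenses, or that the recruiting investigator learns each arm before the next enrolment. Written consent precedes enrolment, all eligible patients are to be documented and invited, and list position follows arrival for the baseline examination. A journal article may also leave envelopes or central release to the full protocol.

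Much of this stands. The missing description of a release procedure is not itself a finding. Documenting all eligible patients limits selective invitation, though not timing. Because the outcome is a change from baseline, part of any selection on baseline severity may be absorbed. What does not stand is the idea that a better-guarded list would cure the problem: with visible treatment and blocks of two, the second of each pair can be deduced without it.

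Three stronger readings are tempting, but the documents do not support them:
- **Nothing is concealed.** The first of each pair remains 50/50 to anyone without the list, and the trial is not wholly unblinded.
- **The nurse leaks or uses the list.** No section says that the nurse assistant recruits, screens or shares it. The location of the list is a risk, not a demonstrated breach.
- **Assessor blinding fails through pairing.** Assessors work from codes and images are sent anonymously. The code format is not given, and nothing shows that assessors could tell who is paired with whom.

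**Conclusion.** The point holds for the block size. Blocks of two with visible treatment leave up to 23 of 46 allocations (50%) known in advance to a recruiter who knows the preceding arm, with 75% of best guesses correct. For those participants, the statement under Concealment mechanism {16b} that allocation is hidden from investigators is not secured. The 50% and 75% figures are exact. They rest on one condition: that the preceding arm is known before the next participant is enrolled. This is a reasonable inference from one clinic, sequential assignment by arrival and staff who cannot be blinded, but the article does not state it of the recruiting investigator.

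The consequence is a possibility, not a prediction. A reader might take the 27% type I error as the expected damage; it is the extreme of the scenarios, with every foreseeable participant steered by 2 points. With one third steered by 1 point it is about 6%. Since selection at enrolment cannot be reliably removed in the analysis, the design should be changed while participants remain to be randomised.

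**What to change.** - Replace fixed blocks of two, under both Trial design {8} and Sequence generation {16a}, by randomly permuted blocks of varying size, for example a random mix of 4 and 6.
- Let only the non-research person who generates the list know the sizes used and their order, and print neither in any site-facing document. Publishing an exact composition would defeat the purpose.
- Keep the list outside the recruiting clinic.
- Release assignments one at a time, by sequentially numbered sealed opaque envelopes or a phone call, and only after consent, eligibility and the baseline assessment are recorded.
- If recruitment has begun, apply this to all remaining participants.

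The cost is a new list, a release procedure and a short amendment. Arm sizes may differ by up to 3 (half of a block of 6) if recruitment stops mid-block. The main gain is that very few allocations remain certain; the best-guess rate falls only from 75% to about 69%.
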